We present the protocol for a superiority, prospective, monocentric, randomized, phase II controlled trial with a 2:1 parallel group design. The primary objective of this trial is to evaluate the impact of osteopathic visceral mobilizations on postoperative quality of life in women undergoing surgery for endometriosis. Intervention includes postoperative consultations with an experienced osteopath and training in abdominal self-mobilization, with outcomes assessed at 12 months post-surgery. Secondary objectives include comparing patient quality of life at 6 and 12 months post-surgery, post-operative pelvic pain, scar appearance, abdominal flexibility, range of medical and non-medical care, use of analgesics and hormonal treatments, pregnancy achievement documented at 12 months, physical activity and sedentary lifestyle and patient compliance throughout the study.

This protocol provides a robust framework for investigating the effectiveness of osteopathic interventions in improving postoperative outcomes and quality of life in this patient population.

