### Outcomes

The primary outcome is the percentage variation in baseline EHP30 questionnaire scores between the pre-operative visit and at 1 year after surgery.

To measure QoL, the authors chose the EHP-30 questionnaire, one of the most frequently used scales for quantification of perceived health, specific to endometriosis [11].

The EHP-30 contains 30 items ranging from 0 (best health status) to 100 (worst health status). The core questionnaire items are grouped into 5 main scales: pain (11 items), control and powerlessness (6 items), emotional well-being (6 items), social support (4 items) and self-image (3 items). A modular questionnaire, that may not apply to all women with endometriosis, comprises 23 items grouped into six scales: ‘Work’ (5 items), ‘Relationship with children’ (2 items), ‘Sexual intercourse’ (5 items), ‘Medical profession’ (4 items), ‘Treatment’ (3 items), and ‘Infertility’ (4 items) [7].

Secondary outcomes are listed below:

1/- a/The following validated questionnaire scores: EHP-30, GIQLI (digestive function), FSFI (sexual function), ICIQ-FLUTS (urinary tract symptoms) and PCS (pain catastrophizing) evaluated at the pre-operative visit, and at 6 and 12 months.- b/VAS of pelvic pain reported at the pre-operative visit, then post-operatively at H6, D1, 1 month, 6 and 12 months and expressed as a percentage variation compared with pre-operative visit results.-c/Post-operative examination of scar appearance by the surgeon at 6 and 12 months using the SCAR (Scar Cosmesis Assessment and Rating) scale.2/- a/VAS of abdominal flexibility in the following areas: hypogastrium, and right and left iliac fossa, at one year assessed by an independent osteopath, scores ranging from 0 to 10 (0 corresponding to normal flexibility and 10 to total rigidity).- b/Consultations in addition to conventional care (medical and non-medical)- c)Use of analgesics and hormonal treatments reported by patients during the first postoperative year-d)Pregnancy achievement during the first postoperative year3/The International Physical Activity Questionnaire (IPAQ) assessed before surgery, at 6 and 12 months after surgery.4/Short-term compliance in terms of number of days and frequency of mobilizations, assessed on a weekly basis for up to 6 weeks,. Long-term compliance is assessed monthly post-cycle in terms of whether and how often mobilizations were performed, and if used in cases of pain.

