The main analysis will be based on a comparison between the experimental and control groups using a Student’s t test or a Wilcoxon test according to distribution (Gaussian or not). Results will be expressed in terms of effect size and associated 95% confidence intervals.

The main analysis will be supplemented by a multivariate analysis of the linear regression type, to take into account covariates selected on the basis of univariate analysis results and their clinical relevance, including age, contraception and previous use of osteopathic mobilization. If necessary, the dependent variable under study may be modified. Particular attention will be paid to the study of multicollinearity (Farrar and Glauber test and VIF indicator) and to the conditions of the model application, notably the normality of residuals. Results will be expressed in terms of regression coefficients and 95% confidence intervals. Subgroup analyses will be proposed for the primary endpoint. The group x subgroup interaction, derived from the linear model described for the main multivariate analysis, will be analyzed and the result expressed in terms of associated regression coefficients and 95% confidence intervals.

Changes in quantitative evaluation criteria (secondary objective 1) based on longitudinal data (measurements repeated over time) will be studied using linear mixed models. These models take into account the correlation of measurements for the same patient. The patient will therefore be considered as a random effect in the model. Time will be considered as both a fixed and a random effect, with dependent variable transformation if necessary. Multivariate models will be considered. The comparison between the two randomization groups will be evaluated by adding the group and its interaction with time as fixed effects to the model. Models can be adjusted for age and contraception, and variable selection can be performed. Results will be expressed in terms of regression coefficients and 95% confidence intervals. Similarly, developments in qualitative evaluation criteria (secondary objective 4) will be based on generalized mixed models of the logistic type. Results will be expressed in terms of odds ratio and 95% confidence intervals.

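### Pelvic-pain VAS as percentage variation from baseline has no value at a pre-operative score of 0 and is unstable at low scores; raw VAS adjusted for baseline would avoid this

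*Protocol article*

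**What the plan says.** - **Outcome.** In the Outcomes section, item 1b takes the pelvic-pain VAS before surgery, "then post-operatively at H6, D1, 1 month, 6 and 12 months and expressed as a percentage variation compared with pre-operative visit results".
- **Model.** Statistical methods assigns this group of outcomes to a mixed model: "Changes in quantitative evaluation criteria (secondary objective 1) based on longitudinal data (measurements repeated over time) will be studied using linear mixed models". The patient is a random effect. On time it states: "Time will be considered as both a fixed and a random effect, with dependent variable transformation if necessary". The arms are compared by "adding the group and its interaction with time as fixed effects to the model".
- **Eligibility.** The Population section asks for an indication for surgery for infiltrating endometriosis and excludes superficial disease. It sets no lower limit on pre-operative pain.
- **Objective.** The Introduction reads: "Secondary objectives include comparing patient quality of life at 6 and 12 months post-surgery, post-operative pelvic pain". The two time points there belong to quality of life. Pelvic pain is listed without a target visit.

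The article does not say what happens when the pre-operative VAS is 0, whether time is continuous or categorical, or whether the pre-operative record is itself an outcome row in the model.

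**The concern.** A percentage change divides by the baseline. Where the baseline can be zero, the outcome does not exist for some eligible patients. Where it can be small, the outcome is very large for others. It is also lopsided: the best result is -100%, while the worst has no practical limit. The early visits at 6 hours and one day follow an operation, so a rise from a low elective baseline is plausible exactly there.

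Two things are at stake for the pain result. Patients with little or no pain before surgery are lost, which narrows the population the result describes. Among those who remain, the estimated arm difference may depend on a handful of low-baseline patients.

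A secondary question is how time enters the model. A random effect of time alongside a random patient effect, with one value per patient and visit, suggests a slope. A straight line is a poor description of pain from hours after surgery to one year.

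**Working it through.** The documents state no figure for the pelvic-pain VAS, so there is none to reproduce. The sample size (63 patients, 42 and 21) is for the EHP-30 and enters only as the number of patients.

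**1. Behaviour of the outcome.** Formula: percentage variation = 100 × (follow-up − baseline) / baseline.

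| Baseline | Follow-up | Result |
|---|---|---|
| 0 | any | undefined |
| 0.5 | 3 | 100 × 2.5/0.5 = +500% |
| 1 | 3 | 100 × 2/1 = +200% |
| 1 | 5 | 100 × 4/1 = +400% |
| 5 | 3 | 100 × (−2)/5 = −40% |
| 8 | 3 | 100 × (−5)/8 = −62.5% |
| any above 0 | 0 | −100%, the floor |

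The same follow-up score of 3 runs from −62.5% to +500% depending only on the baseline.

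**2. Weight of one patient.** In a plain arm mean with complete data, one patient at +400% rather than 0% moves the mean by 400/21 = 19.0 percentage points in the control arm, or 400/42 = 9.5 in the experimental arm. Four patients with complete relief (4 × −100%) are needed to offset that one.

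**3. Chance of an undefined value.** The share p with pre-operative VAS 0 is an assumption. The expected number is 63p, and the chance of at least one is 1 − (1 − p)^63.

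| p | Expected number | Chance of at least one |
|---|---|---|
| 1% | 0.6 | 47% |
| 2% | 1.3 | 72% |
| 5% | 3.2 | 96% |
| 10% | 6.3 | >99% |

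**4. Coding of time.** Assume true arm differences in percentage variation of 0, 0, −10, −20 and −20 at t = 0.008, 0.033, 1, 6 and 12 months (post-operative visits only). Fit a straight line by least squares:

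- mean t = 19.042/5 = 3.808; mean difference = −50/5 = −10
- slope = −179.58/108.48 = −1.655 per month
- intercept = −10 + 1.655 × 3.808 = −3.70
- fitted difference at 6 months = −3.70 − 6 × 1.655 = −13.6; at 12 months = −3.70 − 12 × 1.655 = −23.6

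A simulated mixed model with the same mean profile (1,500 patients, 2:1, random intercept and random time slope) gave:

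| Fixed part | 6 months (assumed −20) | 12 months (assumed −20) |
|---|---|---|
| linear time | −13.7 | −25.2 |
| categorical visit | −19.1 | −22.2 |

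The categorical estimates agree with the assumed values within simulation error, and the random time slope was kept in both fits. The profiles and variances are illustrative and do not come from the documents.

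**The case against.** The strongest reply has four parts.

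- **Transformation is allowed.** The plan permits the dependent variable to be transformed. That may ease skew, but it cannot create a value where the denominator is zero.
- **No bias between arms.** The pre-operative VAS is a baseline characteristic, so losing patients at 0 does not by itself bias the randomised comparison. That stands. The cost is numbers, generality and instability. The plan also does not say such patients are dropped; without a rule, however, they have no value to analyse.
- **Time coding belongs in an analysis plan.** This largely stands. The silence on coding would not be a finding alone. It is raised only because the same repair settles it.
- **One secondary outcome.** Statistical methods describes certain secondary analyses as mainly exploratory. This limits the weight of the point, not its correctness.

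Three stronger readings are tempting, and the documents do not support them.

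- A reader might infer that the model cannot yield the 6- and 12-month differences. The text never makes time linear and includes the arm-by-time term. Categorical visit gives these differences directly, and even linear time gives values, though distorted ones. The Introduction also ties those two visits to quality of life, not pain.
- A reader might infer that the model contains a baseline point with no variance, because percentage variation is 0 for everyone before surgery. That matters only if the pre-operative record is an outcome row, which the article does not say.
- A reader might extend the point to the questionnaire scores in item 1a and to the IPAQ. Those secondary outcomes are listed as scores or assessments, not as percentage variation.

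**Conclusion.** The point holds for the pelvic-pain VAS. The stated outcome is undefined at a pre-operative score of 0, and nothing in the eligibility criteria excludes that score. At low scores it is unstable and asymmetric, so that one patient going from 1 to 5 can move a 21-patient arm mean by 19 percentage points. These facts follow from the definition and need no assumption about the data. How often they will bite does need one: with 1% to 10% of patients at VAS 0, the chance of at least one undefined patient among 63 runs from 47% to over 99%.

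On time, the conclusion is conditional. If it is coded linearly, the visit differences would be misstated (in the illustration, about −14 and −25 for a true −20 and −20). If visit is categorical in the fixed part, they are not.

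This is a weakness in one secondary outcome. It does not affect the sample size. It is worth correcting because a better analysis of the same data costs almost nothing.

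**What to change.** For secondary outcome 1b only, amend Outcomes and Statistical methods as follows:

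- Analyse the raw post-operative VAS in the linear mixed model, with pre-operative VAS as a covariate and not as an outcome row.
- Enter visit as a categorical fixed effect, with arm and arm-by-visit.
- Report the adjusted arm difference with its 95% confidence interval at each scheduled post-operative visit.
- Keep percentage variation, if wanted, as a descriptive summary, and state how many patients have no value because their baseline is 0.

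The pre-operative VAS is already collected, so no new data, visits or patients are needed. Patients with baseline 0 stay in the analysis. The cost is a change of wording and a few more degrees of freedom for the visit terms.

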### Sample size

The required number of subjects is based on a comparison between the two randomized groups (experimental group *vs*. control) of the percentage variation in EHP-30 questionnaire scores between the pre-operative visit and at 1 year, with a two-sided first-species risk of error of 5%. For ethical reasons, we chose a 2:1 ratio for randomization.

In the literature, Goncalves et al. reported on the evolution of EHP30 scores (before/after) for a control and treatment group receiving an intervention (yoga sessions) [43]. Variations were small in the control group for the 5 main EHP-30 dimensions, and ranged from 20 to 35 points for the treatment group. Pokrzywinski et al [44]. showed the same before/after differences for a control and treatment group (Elagolix molecule), and defined thresholds of between 20 and 35 points for clinically significant differences.

To demonstrate a difference of 20 points associated with a standard deviation of 25, in percentage variation for EHP-30 questionnaire scores between the pre-operative visit and 1 year, with a statistical power greater than 80%, 38 patients are required in the experimental group and 19 in the control group. To allow for patients leaving the protocol and loss to follow-up, 10% more patients are required in each group. Thus, a total of 63 patients will be recruited (42 in the experimental group and 21 in the control group).

### Randomization

Patients will be randomly assigned to the two groups using REDCap® software, with a 2:1 ratio.

### Data collection methods

Data will be collected using 2 different tools: REDCap® electronic data capture and the NoEndo platform. An eCRF (electronic Case Report Form) using REDCap® will be used by the surgeon and clinical research associates to collect patient clinical data at each visit, as per the protocol, i.e., demographic and relevant background data, surgical indication, scar examination, pain assessment, postoperative complications, sick leave, hormonal treatment and follow-up data during the 1^st^ year following surgery for each group. This data concerns abdominal self-mobilizations for the experimental group, and abdominal flexibility and extent of medical and non-medical treatment for both groups. Quality-of-life data will be measured using questionnaires specific to endometriosis (EHP-30, GIQLI, FSFI, ICIQ-FLUTS and PCS), which patients will complete via the platform NoEndo. Comparison of the different scores obtained pre-operatively and at 6 and 12 months post-operatively will enable analysis of changes in quality of life.

### Data management

#### Data quality.

Study data will be collected and managed using REDCap electronic data capture tools (version 13.1.28., Vanderbilt University) hosted at Clermont-Ferrard UHC [45,46]. REDCap (Research Electronic Data Capture) is a secure, web-based software platform designed to support data capture for research studies, providing 1) an intuitive interface for validated data capture; 2) audit trails for tracking data manipulation and export procedures; 3) automated export procedures for seamless data downloads to common statistical packages; and 4) procedures for data integration and interoperability with external sources. Data entry is secured by encryption and a login and password for each user. Data will be collected when obtained and an explanation provided for any missing data.

The NoEndo ISO certified platform provides a double authentication system for patients and health professionals, accessible via the Internet and an application (available for android). To avoid missing data, a number of key items are mandatory, preventing patients from saving an entry page should an answer be missing. Coherence testing and outlier detection implemented on the platform ensures data quality and avoidance of outliers.

All data will be monitored according to specifications defined for this type of study, with special attention paid to limiting missing data.

#### Data privacy.

All subject data collected and transmitted to the sponsor by the investigators (or any other specialist) will be rendered anonymous.

Only the first letter of the subject’s first name and surname will be recorded, together with a specific coded number to indicate the order of subject inclusion.

The sponsor will ensure that all subjects taking part in the research provide written consent for access to individual data, and that strictly necessary for research quality control.

On REDCap® and NoEndo, an anonymous number will be assigned to each patient. For database interoperability (eCRF REDCap® and NoEndo) and to guarantee data confidentiality, NoEndo anonymous numbers will be communicated to REDCap®.

### Statistical methods

Statistical analyses will be carried out using R software (R Core Team (2022). R: A language and environment for statistical computing. R Foundation for Statistical Computing, Vienna, Austria. URL https://www.R-project.org/.).

Descriptions are given in number (N) and percentage (%) for qualitative variables, and in mean and standard deviation (SD) or median and interquartile range for quantitative variables, according to their distributions (Gaussian or not). Missing data will be quantified. Normality will be analyzed using the Shapiro-Wilk test and histograms.

Patients will be described and compared between groups at inclusion according to compliance with eligibility criteria, epidemiological characteristics and clinical features. A description of protocol deviations, patients allocated according to these deviations and reasons for drop-out will also be provided.

Initial comparability of the two groups will be assessed on the main patient characteristics and potential factors associated with the primary endpoint. Any difference between the two groups relating to these characteristics will be determined on the basis of clinical and statistical considerations.

Comparisons between groups will be made systematically 1) without adjustment 2) by adjusting for those factors for which distribution may be unbalanced between groups despite randomization, such as contraception, level of disease severity and post-operative complications. All statistical tests will be performed using a two-sided alpha level of 5%. Certain analyses involving secondary endpoints will be mainly exploratory in nature. As discussed by Feise et al. [47] adjustment of alpha risk will not be proposed systematically, but on a case-by-case basis in the light of clinical and statistical considerations.

The main analysis will be carried out on an intention-to-treat basis. An intention-to-treat population refers to all randomized patients except those for whom consent is not obtained or who withdraw their consent concerning use of their data. A per-protocol analysis will be considered of all randomized patients except for those with one or more major deviations defined as: patients ineligibility, uncompliant patients in the experimental group (less than once a day on average over the first post-operative month), or control group patients who perform visceral mobilizations more than 4 times during the year of their own initiative.

The main analysis will be based on a comparison between the experimental and control groups using a Student’s t test or a Wilcoxon test according to distribution (Gaussian or not). Results will be expressed in terms of effect size and associated 95% confidence intervals.

The main analysis will be supplemented by a multivariate analysis of the linear regression type, to take into account covariates selected on the basis of univariate analysis results and their clinical relevance, including age, contraception and previous use of osteopathic mobilization. If necessary, the dependent variable under study may be modified. Particular attention will be paid to the study of multicollinearity (Farrar and Glauber test and VIF indicator) and to the conditions of the model application, notably the normality of residuals. Results will be expressed in terms of regression coefficients and 95% confidence intervals. Subgroup analyses will be proposed for the primary endpoint. The group x subgroup interaction, derived from the linear model described for the main multivariate analysis, will be analyzed and the result expressed in terms of associated regression coefficients and 95% confidence intervals.

Changes in quantitative evaluation criteria (secondary objective 1) based on longitudinal data (measurements repeated over time) will be studied using linear mixed models. These models take into account the correlation of measurements for the same patient. The patient will therefore be considered as a random effect in the model. Time will be considered as both a fixed and a random effect, with dependent variable transformation if necessary. Multivariate models will be considered. The comparison between the two randomization groups will be evaluated by adding the group and its interaction with time as fixed effects to the model. Models can be adjusted for age and contraception, and variable selection can be performed. Results will be expressed in terms of regression coefficients and 95% confidence intervals. Similarly, developments in qualitative evaluation criteria (secondary objective 4) will be based on generalized mixed models of the logistic type. Results will be expressed in terms of odds ratio and 95% confidence intervals.

Comparisons at 1 year will be made using standard statistical tests visit (secondary objective 2). To investigate the dependence between two qualitative variables (including randomization group and fertility), the Chi2 test or Fisher’s exact test (depending on subject numbers) will be applied to a qualitative variable. To compare a quantitative variable (including abdominal flexibility) with a two-modality qualitative variable (including randomization group), a t-test or a Wilcoxon test will be applied, depending on distribution (Gaussian or not).

To identify patient profiles based on the sub-domains of quality of life assessed during the pre-operative visit (secondary objective 3), a factorial analysis will be carried out, followed by a classification method. A Principal Component Analysis (PCA) will be used for further detailed analysis of quantitative data. A hierarchical ascending classification (HAC), based on the results of the factorial analysis will then be carried out. To compare these different groups in terms of improvement in post-operative quality of life, analysis will be based on a comparison using a Student’s t test or a Wilcoxon test according to distribution (Gaussian or not) if classification results in a typology of 2 groups, or using an ANOVA or a Kruskal-Wallis (according to distribution) if classification results in a typology of more than 2 groups.

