### Study design and participant timeline

The flow chart of the study is presented in **Fig 1**. This is a superiority monocentric 2:1 randomized parallel group trial comparing reported quality of life, using the 30-item Endometriosis Health Profile (EHP-30) questionnaire, in 2 groups of patients operated for endometriosis. In the experimental group, patients receive pre and post-operative osteopathic consultations. The pre-operative consultation includes learning abdominal self-mobilizations and abdominal diaphragmatic respiration with the osteopath. The 5 post-operative consultations, occurring at 3–5 day intervals, involve visceral mobilizations performed by the osteopath (D6, D10, D14, D18 and W6). In the second group (control group), patients receive no osteopathic mobilizations (**Fig 2**).

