#### Osteopathic interventions.

Patients in the experimental group will receive training in abdominal self-mobilizations at an initial pre-operative consultation, to ensure they can perform these techniques independently and take an active role in their treatment. While some maneuvers remain managed by the osteopath, patients are required to perform frequent sessions of self-mobilization of the abdomen, combined with Abdominal Diaphragmatic (AD) breathing. AD breathing, the self-mobilization procedure and osteopathic intervention are detailed in appendix 1 and 2.

Patient participation allows:

Optimization of treatment provided by the osteopath, who cannot be seen every dayPain management using the simple tools available to patientsAssociation of this part of the body with sensations other than painPatients to take an active role in their treatment.

Patients in the intervention group receive six sessions with the osteopath.

**Session 1** Pre-surgical session focusing on the teaching of self-mobilization **(****Appendix 1**)

AD breathing in 6 stepsAbdominal self-mobilization of:Three lower abdominal regions: right iliac fossa, hypogastrium and left iliac fossaAbdominal scarsSequence of maneuvers and repetitions:Ten AD breathsAbdominal self-mobilizations (of the 3 regions + scars)10 AD breaths

The procedure is to be repeated 3 times a day during the first month.

In the first postoperative week if self-mobilizations are difficult to perform (e.g., high pain levels or apprehension), the patient will perform AD breathing more frequently, namely 6 cycles of 10 AD breaths per day.

**Sessions 2–6** (D6, D10, D14, D18 and W6): Visceral mobilizations by the osteopath are performed during the month following surgery, with sessions at 3–5-day intervals (Appendix 2, **Fig 1** and **Fig 2**).

During these consultations, the osteopath ensures self-mobilizations are being correctly carried out, readjusts if necessary and answers any patients questions. The osteopath also checks that patient follow-up notebooks are completed.

These sessions also involve:

a/Achieving a balanced diaphragmatic rangeb/General abdominal mobilizations: hypogastric zones and right and left iliac fossaec/Abdominal scar manipulationd/Maneuver stages:Ten AD breathsWork on achieving balance in diaphragmatic rangeGeneral abdominal mobilizationsTen AD breaths

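### The adjusted group comparisons include post-operative complications, which arise after allocation and may be changed by the intervention, so the adjusted estimate can depart from the total effect

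*Protocol article*

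**What the plan says.** The Statistical methods section of the protocol article sets a general rule, which opens: "Comparisons between groups will be made systematically 1) without adjustment 2) by adjusting for those factors". As examples of what to adjust for, the rule lists items "such as contraception, level of disease severity and post-operative complications". Complications thus stand in the same list as contraception and disease severity, under a rationale of chance imbalance ("for which distribution may be unbalanced between groups despite randomization").

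The same section makes the main analysis an unadjusted Student's t or Wilcoxon test on the intention-to-treat population. A linear regression supplements it. The covariates named there are age, contraception and previous osteopathic mobilisation; complications are not named, but the list is open. For the mixed models it says: "Models can be adjusted for age and contraception, and variable selection can be performed".

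On timing, Study design and participant timeline describes the experimental arm: "The pre-operative consultation includes learning abdominal self-mobilizations and abdominal diaphragmatic respiration with the osteopath". Osteopathic interventions asks for self-mobilisation three times a day in the first month, provides for the case "In the first postoperative week if self-mobilizations are difficult to perform", and places the osteopath's sessions at D6, D10, D14, D18 and W6. Surgical technique has the surgeon assess complications at 6 weeks, 6 months and 12 months.

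**The concern.** Adjusting for imbalance despite randomisation makes sense only for variables that allocation cannot influence. A post-operative complication occurs after allocation and while the arms differ in abdominal and scar mobilisation. The Introduction argues that such mobilisation alters post-surgical healing: it is meant to disrupt forming adhesions and speed the absorption of fluid, and ileus prevention is mentioned as a possible benefit. On that reasoning a complication may be a consequence of treatment.

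Conditioning on such a variable has two effects. It takes out whatever part of the treatment effect runs through complications. It also makes patients with the same complication status non-comparable between arms if an unmeasured factor, such as frailty, drives both complications and quality of life. The rule has an awkward trigger as well: a true effect of the intervention on complications makes them more likely to look unbalanced, and that is when adjusting for them misleads.

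At stake is the reading of the adjusted result that is to accompany each unadjusted comparison.

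**Working it through.** **Order of events.**

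| Step | Where stated | Timing |
|---|---|---|
| Arm-specific teaching session | Study design; Osteopathic interventions | before surgery |
| Self-mobilisation, experimental arm | Osteopathic interventions | from the first post-operative week, through the first month |
| Osteopath sessions | Study design; Osteopathic interventions | D6 to W6 |
| Complications assessed | Surgical technique | 6 weeks, 6 and 12 months |
| Complications used for adjustment | Statistical methods | as if a baseline imbalance |

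The article does not date randomisation. That it precedes surgery is inferred from the pre-operative session given to one arm only.

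**The plan's own figures.** No figure attaches to this rule. The sample size gives the scale. With difference 20, SD 25, two-sided 5%, 80% power and 2:1 allocation, the control arm needs (1 + 1/2) × (1.960 + 0.842)² × 25²/20² = 18.4, so 19 control and 38 experimental, as stated. The standard error of the unadjusted difference is 25 × √(1/38 + 1/19) = 7.0 points.

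**Size of the shift without shared frailty.** Let pC and pE be the complication risks in the control and experimental arms, b the points of improvement lost per complication, and d the direct effect (positive = improvement).

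- Total effect = d − b(pE − pC)
- Effect adjusted for complications = d
- Shift = b(pE − pC)

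With b = 15 and risk rising from 15% to 30%: 15 × 0.15 = +2.25. With risk falling from 15% to 5%: 15 × (−0.10) = −1.5. With equal risks: 0.

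**With shared frailty.** No simple formula applies, so this was simulated with 2,000,000 patients at 2:1. Frailty U is standard normal, adds U to the log-odds of a complication and takes 10U points off improvement. The outcome SD before the complication effect is 25. All complication inputs are assumptions; none is in the documents.

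| Risk, control → experimental | b | d | Frailty | Total effect | Adjusted | Shift |
|---|---|---|---|---|---|---|
| 15% → 15% | 15 | 20 | no | 20.0 | 20.0 | 0.0 |
| 15% → 30% | 15 | 0 | no | −2.3 | −0.1 | +2.3 |
| 15% → 5% | 15 | 20 | no | 21.5 | 20.0 | −1.5 |
| 15% → 30% | 0 | 0 | yes | 0.0 | +1.3 | +1.3 |
| 15% → 30% | 15 | 0 | yes | −2.2 | +1.4 | +3.5 |
| 30% → 15% | 15 | 20 | yes | 22.2 | 18.7 | −3.5 |
| 15% → 30% | 25 | 20 | yes | 16.3 | 21.3 | +5.0 |

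Entries are rounded separately and carry simulation error of up to about 0.1. The second row shows a small harm disappearing and the fifth shows a sign reversal. The third and sixth show benefit being removed. The last row needs a doubled risk, a 25-point cost per complication and shared frailty together.

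Smaller changes give smaller shifts. In a second model (15 points per complication, 8 points per SD of frailty) with a control risk of about 10%, an odds ratio of 2 shifts the estimate by about 1.6 points and an odds ratio of 1.3 by about 0.5.

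**The case against.** The strongest reply is that the primary inference is untouched. The main test is unadjusted and by intention to treat, and the rule puts the unadjusted comparison first each time, so the total effect is always visible beside the adjusted one. The supplementary regression does not name complications. No passage says that mobilisation raises or lowers surgical complications, and if it does neither, adjusting is harmless. Most of the shifts tabulated are at most half of the 7.0-point standard error. All of this stands, and it limits the weight of the point. It does not rescue the rule: the trial cannot know in advance that complications are unaffected, and the stated rationale does not fit a post-allocation event.

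A reader might also infer that adjusting for contraception is the same error, because "Use of analgesics and hormonal treatments reported by patients during the first postoperative year" is a secondary outcome. The documents do not support that. Nowhere do they say that a post-operative value is used, and contraception is listed beside age and previous osteopathy, which reads as baseline. Stating the time point is a useful precision, not the correction of an error.

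**Conclusion.** The point holds in a limited form. Naming post-operative complications as an adjustment factor is wrong as written, because it treats a possible consequence of treatment as a chance imbalance. A reader might conclude that the adjusted effect is biased, or that the trial's main result is compromised. Neither follows. Bias arises only if the intervention changes complications, its direction can go either way, and the main unadjusted test is not involved.

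Under the assumed inputs the shift is 0 to about 5 EHP-30 points in absolute size, up to a quarter of the 20-point target (5/20). That range rests on assumed complication risks of 5% to 30%, a cost of 0 to 25 points per complication, and frailty either absent or of the strength stated. It also rests on the inference that allocation precedes surgery. This should be fixed; it is not an obstacle to the trial.

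**What to change.** In Statistical methods, delete post-operative complications from the examples of adjustment factors. State that adjusted comparisons use only variables the intervention cannot affect, with contraception taken at its pre-operative value. Disease severity need not be removed on this ground: it is staged after surgery but describes disease already present.

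Report post-operative complications by arm as an outcome; they are already collected at the surgeon's visits. If a model that conditions on complications is still wanted, label it exploratory and do not present it as an estimate of the overall treatment effect.

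The cost is a sentence or two. The sample size stays at 38 + 19 evaluable and 63 recruited, no data are added and no patient is affected. With data collection planned to January 2028, the change can be made before any analysis.
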